## Abstract

**Introduction:**

Outdoor active play is essential for children’s health, well-being and holistic development. However, there is a lack of high-quality evidence on effective sustainable and scalable interventions that leverage outdoor play and environmental affordances to promote physical literacy, including motor competence, physical activity, engagement and motivation for movement in early childhood. In particular, limited research has examined how outdoor kindergarten environments can be intentionally used and optimised to support diverse forms of active play through social and other potential affordances, nor how educators can be supported to facilitate such processes. The PLAY UP project aims to address this gap by investigating how a co-created, affordance-based intervention, developed in collaboration with children and supported by educator training, can enhance preschool children’s engagement in active play and multidimensional development in outdoor kindergarten settings.

**Methods and analysis:**

This study describes the protocol of a cluster-randomised trial to be conducted in Portugal, involving three kindergartens and up to 215 preschool children, their educators and parents. The protocol includes an initial pilot phase (approximately 75 children from one kindergarten) to assess feasibility, acceptability and implementation procedures, followed by a main study phase with intervention and wait-list control clusters. The intervention comprises 15 sessions delivered in outdoor kindergarten settings. PLAY UP adopts a multidimensional and multimethod approach combining quantitative and qualitative methods. Outcomes related to physical literacy, including physical activity, motor competence, engagement, enjoyment and motivation for movement, are assessed using questionnaires, standardised tasks, accelerometry, Global Positioning System-based positioning technologies and systematic observations, complemented by interviews. Data will be analysed using cluster-aware statistical models and integrative mixed-methods approaches.

**Ethics and dissemination:**

This study has been approved by the Ethics Committee of the University of Évora (Ref. #24101). Written informed consent was obtained from parents or legal guardians, and all data will be handled confidentially in accordance with ethical and data protection standards. Study findings will be disseminated through open-access peer-reviewed publications, scientific conferences and knowledge-transfer activities targeting education professionals and relevant stakeholders.

**Trial registration number:**

NCT07355179.

STRENGTHS AND LIMITATIONS OF THIS STUDYCluster-randomised trial design conducted in real-world kindergarten settings, enhancing ecological validity and relevance for early childhood education practice.Affordance-based, co-created intervention, developed with children and supported by educator training, addressing both environmental and pedagogical determinants of physical literacy.The limited number of clusters may constrain statistical power and generalisability at the cluster level, despite an adequate individual-level sample size.The context-specific nature of outdoor kindergarten environments may limit transferability to settings with different spatial, cultural or pedagogical characteristics.Outdoor-based physical activity assessments may be influenced by seasonal and weather-related variability, potentially affecting interpretation of movement-related outcomes.

## Introduction

Physical literacy (PL) has been conceptualised as a holistic and multidimensional construct that extends beyond the development of motor skills alone. It encompasses physical competence, physical activity (PA), motivation, confidence, as well as knowledge and understanding, enabling individuals to engage in PA throughout the lifespan.^1 2^ In addition to these dimensions, PL integrates affective and cognitive components related to PA, reinforcing its comprehensive nature.^3^ From a theoretical perspective, PL is grounded in embodied and relational approaches, which conceptualise movement as central to how individuals interact with and make sense of their environment.^4^ In this sense, physically literate children develop motor competence and acquire diverse movement experiences through engagement with a variety of environments (eg, land, snow or ice, water or air), contexts (eg, play, movement or sport experiences), and social agents (eg, educators, peers).^5^ To foster PL, children need to engage in varied and enjoyable PA that promotes positive emotions, meaningful experiences, sustained motivation for movement and a meaningful connection with their environment^6^.

In early childhood, a critical period for development, meaningful movement experiences and supportive pedagogical environments are essential for fostering PL^7^. In this context, active play emerges as a key means through which children develop physical, cognitive and socioemotional competencies. In kindergarten settings, outdoor active play refers to spontaneous, unstructured and often vigorous movement involving gross motor or whole-body activity in which young children freely choose enjoyable ways to expend energy^8^; it has been identified as a particularly powerful approach to fostering PL while supporting motor, socioemotional and cognitive development,^9^ engagement in outdoor play has been shown to support motor skills development,^10^ executive functioning,^11^ promote social behaviour and peer interactions^12^ and contribute to overall well-being, learning and holistic development.^13^ The effectiveness of outdoor active play is closely linked to the characteristics of the environment in which it occurs. Kindergarten outdoor spaces play a crucial role in fostering PL, PA, play, peer interaction and meaningful engagement with the surrounding environment.^14–16^ These environments are inherently rich in affordances, defined as possibilities for action^17^, which support exploration, interaction and movement, thereby contributing to children’s cognitive, linguistic, socioemotional and physical development.^13 18^ A physically literate child is able to interpret the environment and identify affordances,^19^ including both physical and social affordances, where objects, materials, spaces and peers provide opportunities for interaction.^20^ The characteristics of these affordances play a key role in shaping children’s PA behaviours and social engagement,^21^ while specific features of outdoor environments create opportunities for active play and interaction.^22^ Through engagement with outdoor environments, children explore and actualise affordances,^14^ progressively develop motor competence and body control^18 23^ and enhance self-regulatory and relational skills.^13 24^

Beyond developmental outcomes, outdoor environments also provide important physiological and health benefits. Exposure to natural elements such as sunlight and fresh air promotes PA and contributes positively to health, well-being, learning and development.^13 25^ Outdoor play supports vitamin D synthesis and serotonin regulation, contributing to immune function and mental health,^13^ while environmental variability enhances sensory integration and musculoskeletal development.^26^ Additionally, active outdoor play has been associated with more favourable movement behaviour patterns, including higher levels of PA and reduced sedentary time,^27^ as well as a reduced risk of myopia and its progression in children.^28^ Recent evidence further highlights the broad benefits of outdoor experiences in early childhood education settings, including improvements in behavioural regulation, learning outcomes, executive functioning, social and emotional skills and attention-related behaviours.^29^ Moreover, greater frequency of outdoor play has been associated with enhanced emotional intelligence and socioemotional development.^30^

Despite these benefits, children’s opportunities for active play have declined, increasingly replaced by sedentary indoor activities. Consequently, prolonged time spent in indoor environments raises concerns about air quality, as kindergarten settings often contain chemical pollutants that may impact children’s neurodevelopment and overall health.^31^ In Portugal, this decline is particularly alarming, raising growing concerns. Schools, which should serve as pivotal settings for encouraging outdoor active play, are no longer actively promoting outdoor activities.^32^ This is particularly alarming given that Portuguese preschoolers spend approximately 40 hours per week in kindergarten,^33^ where they should have ample opportunities to engage in outdoor PA and active play. This period is also critical for motor development, as children are expected to reach the mature stage of fundamental movement skills by around 7 years of age, highlighting the central role of early childhood education in providing sufficient opportunities for practice and skill development.^34^ While outdoor play is deeply embedded in the culture of Nordic countries and widely encouraged in early childhood education, in Portugal it is still perceived mainly as a break time rather than an integral part of learning and development.^35^ Furthermore, most outdoor spaces in Portuguese kindergartens lack essential features to provide preschoolers with meaningful play opportunities.^32^ These spaces often have reduced access to play resources, limited loose objects and materials, as well as a scarcity of natural areas and diverse surfaces.^35^ Another challenge is the predominantly sedentary nature of preschoolers’ PA levels, with only about one in three meeting the recommended PA guidelines^36^ despite outdoor spaces being organised mainly to promote PA and motor and active play,^35^ and despite Portugal’s favourable climate which allows children to be outdoors year-round.

Research has shown that outdoor play interventions improve preschoolers’ motor and socioemotional competences.^23 24^ These interventions can leverage environmental affordances in outdoor kindergarten settings to facilitate active play engagement, as they are well-suited to reach most children and provide an optimal opportunity to promote both PA and active play.^14^ In Portugal, research on intervention-based outdoor play programmes remains scarce, with most studies prioritising indoor activities. While some studies characterise outdoor play environments,^35 37^ randomised trials are limited, highlighting the need for high-quality, scalable interventions to foster PL.

To date, no studies in Portugal have examined the impact of active play on PL in outdoor settings, particularly concerning environmental affordances for exploratory movement experiences. As a result, the existing evidence is insufficient to support evidence-based decision-making for the development of effective programmes and policies.

To address these challenges, the PLAY UP intervention was designed as a co-created, affordance-based approach to foster PL in preschool children through active play in outdoor kindergarten settings. In this context, the present study aims to:

(1) evaluate the effectiveness of the PLAY UP intervention: a co-created, affordance-based approach combined with educator training, in promoting PL in preschool children; (2) examine its effects on PA, motor competence, executive functioning, and social, emotional, and behavioural competences, as well as to explore children’s movement patterns and interactions in outdoor environments and (3) assess the feasibility, acceptability and implementation of the intervention during the pilot phase.

Together, these findings may inform the design of evidence-based, scalable interventions and contribute to public health and educational strategies aimed at promoting PL from early childhood.

## Methods and analysis

### Study design

This study is a cluster-randomised trial, with randomisation at the kindergarten (KG) level, to be conducted in public preschools in Évora, Portugal. The trial includes three KG (clusters). One cluster (four classrooms) is being used in an initial pilot phase to assess feasibility, acceptability and implementation procedures. Following the pilot phase, the intervention will be implemented in the remaining two clusters (three classrooms each), with one assigned to the intervention condition and the other serving as a wait-list control group. The study follows a preintervention and postintervention assessment design. After the pilot phase, the two remaining KG will be randomised at the cluster level in a 1:1 ratio, with one allocated to the intervention group and the other to the wait-list control group. The random allocation sequence will be generated by an independent researcher not involved in recruitment, intervention delivery or outcome assessment, using a computer-generated randomisation procedure. Given the small number of clusters, simple randomisation will be used. The allocation will then be communicated to the research team responsible for implementing the intervention.

The initial pilot phase involves approximately 75 children from one KG, designed to assess the feasibility, acceptability and implementation procedures of the PLAY UP intervention.

The study commenced in January 2026 with recruitment and is currently ongoing, with completion scheduled for the end of June 2027. The intervention phase will consist of 15 sessions per classroom delivered over approximately 8–10 weeks, followed by postintervention assessments. The main comparative study phase will be implemented after completion of the pilot phase, following the same procedures.

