### Sample size

The protocol includes an initial pilot phase involving approximately 75 children to assess feasibility, acceptability and implementation procedures.

For the main comparative phase, sample size was estimated using G*Power (F tests: analysis of variance repeated measures, within–between interaction). Assuming a moderate effect size (f=0.25), α=0.05, power=0.80, two groups, two measurement occasions (baseline and postintervention), a correlation among repeated measures of 0.50 and ε=1, the required total sample size was 34 children.

The overall recruited sample exceeds this individual-level requirement. Given the study design and the limited number of KG clusters in the comparative phase, findings related to intervention effects will be interpreted with caution, and effect estimates with CIs will be reported to support interpretation and inform future sample size assumptions.

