### Data analysis

Data analysis will be conducted using an integrative mixed-methods approach, combining quantitative and qualitative data, and will be performed separately for the pilot phase and the main study phase.

For the pilot phase, feasibility and acceptability indicators will be analysed descriptively, including recruitment, retention and attendance rates, as well as indicators related to implementation, resources and safety. Preliminary changes between baseline and postintervention will be explored using within-group comparisons, as appropriate.

For the main study phase, quantitative outcomes will be analysed by comparing the intervention and wait-list control groups at baseline and postintervention. The choice of statistical tests will be guided by the distribution and characteristics of the data. Where assumptions for parametric analyses are not met, non-parametric tests will be used to compare baseline differences between groups and changes from baseline to postintervention between groups.

Effect sizes will be calculated and reported to support interpretation of findings. The specific metric used will depend on the statistical tests applied, and effect sizes will be interpreted according to established guidelines. Results will be presented as means and SDs or means and 95% CIs, as appropriate.

All statistical analyses will be conducted using a significance level of p<0.05.

Qualitative data, including interviews and observational data, will be analysed using thematic analysis, and findings will be integrated with quantitative results to support interpretation of feasibility, acceptability and intervention effects.

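### With one kindergarten per arm, kindergarten-specific change cannot be separated from the intervention, so the effectiveness aim and the p<0.05 between-arm tests are not supported by the design

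*Protocol article*

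**What the plan says.** The Study design section sets the unit of randomisation: "This study is a cluster-randomised trial, with randomisation at the kindergarten (KG) level". It then assigns the clusters: "The trial includes three KG (clusters). One cluster (four classrooms) is being used in an initial pilot phase". After the pilot, "the two remaining KG will be randomised at the cluster level in a 1:1 ratio", "with one assigned to the intervention condition and the other serving as a wait-list control group". Each of these two kindergartens has three classrooms. The Data analysis section keeps the pilot and the main phase apart, so the pilot kindergarten adds no cluster to the comparison.

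The first aim in the Introduction is to "evaluate the effectiveness of the PLAY UP intervention". The Data analysis section compares the two groups at baseline and afterwards, including their changes, with tests chosen by the distribution of the data, and adds: "All statistical analyses will be conducted using a significance level of p<0.05".

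The Sample size section derives 34 children from an individual-level repeated-measures ANOVA without an ICC and notes that recruitment exceeds this. Because there are few clusters, it says, "findings related to intervention effects will be interpreted with caution", and effect estimates with CIs will be given. The strengths and limitations list names the small number of clusters as a constraint on power and generalisability.

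**The concern.** A cluster-randomised comparison is valid because variation between clusters within an arm shows how far two clusters would differ without any intervention. With one cluster per arm there is no such variation to observe. A change in staff, a local event or a different developmental course in one kindergarten during the intervention period looks exactly like an intervention effect.

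This is a different problem from low power. Low power gives wide but valid intervals. Here a child-level interval or p-value is valid only if the two kindergartens would otherwise have changed by the same amount, and the data cannot test that. The assumption also sits badly with the protocol's own rationale. The Introduction ties the benefit of outdoor play to the particular environment, the educator training is tailored to each kindergarten, and the limitations list calls these settings context-specific.

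At stake is whether a difference between two kindergartens could be reported as a significant effect of the intervention, in a project meant to inform scalable programmes and public health strategy.

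**Working it through.** **Inputs from the protocol article.** Unit of randomisation: kindergarten. Main phase: 2 kindergartens, 1:1 (Study design). Total sample: 215 (Recruitment). Pilot: about 75 (Study design). Sample size inputs: f = 0.25, α = 0.05, power 0.80, two groups, two occasions, correlation 0.50, ε = 1.

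**Assumptions not in the protocol.** An equal split of the main-phase children, and a kindergarten ICC of the baseline-adjusted outcome of 0.01, 0.05 or 0.10.

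**1. The plan's own figure.** For the within–between interaction, λ = f²·N·m/(1−ρ), where m = 2 is the number of occasions. At N = 34, λ = 0.0625 × 34 × 2 / 0.50 = 8.5 on 1 and 32 df, and power is 0.807. At N = 32 power is 0.781. The stated 34 is reproduced, but only for independent children.

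**2. Degrees of freedom.** With c kindergartens per arm, the between-cluster df are 2c − 2. For c = 1 this is 0.

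**3. Randomisation p-value.** There are C(2,1) = 2 possible allocations, so the minimum p is 1/2 = 0.5 one-sided and 2/2 = 1.0 two-sided. The two-sided minimum is 2/C(2c,c): 0.33 for c = 2, 0.10 for c = 3 and 0.029 for c = 4.

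**4. Illustration: children analysed as independent.** Main-phase children: 215 − 75 = 140, about 70 per kindergarten. Design effect: DE = 1 + 69·ICC. True type I error of a nominal 5% test: 2·(1 − Φ(1.96/√DE)). The 95% half-width that allows for the assumed ICC is 1.96·√(2·DE/70). As the number of children grows, it cannot fall below 1.96·√(2·ICC). Both are in SDs of the baseline-adjusted outcome.

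| Assumed ICC | DE | Effective N of 140 | Type I error | Half-width at 70 per kindergarten | Half-width floor |
|---|---|---|---|---|---|
| 0 | 1.00 | 140 | 5% | 0.33 SD | 0 |
| 0.01 | 1.69 | 82.8 | 13% | 0.43 SD | 0.28 SD |
| 0.05 | 4.45 | 31.5 | 35% | 0.70 SD | 0.62 SD |
| 0.10 | 7.90 | 17.7 | 49% | 0.93 SD | 0.88 SD |

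A simulation (10,000 runs, 3 classrooms of 23 children per kindergarten) gave type I errors of 13%, 36% and 50% at the three non-zero ICCs.

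**5. Classrooms as the unit.** A t-test on three classroom means per arm (4 df), in the same simulation with no extra classroom variance, still had type I errors of about 10%, 27% and 40%. Classrooms are nested in the kindergarten and were not randomised, so their scatter does not contain the kindergarten component.

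**6. Cluster-aware models.** A random effect for kindergarten cannot be separated from the arm effect when each arm has one kindergarten. A model with classroom effects only leaves out the level that was randomised.

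**The case against.** Several points on the other side stand.

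- **Disclosure.** The allocation is stated openly, the few clusters are listed as a limitation, and the Sample size section promises caution and estimates with CIs to inform later work. Nothing is concealed, and the plan already leans towards estimation. But neither place says that arm and kindergarten coincide.
- **Change scores.** A reader might infer that every difference in playground, educators or catchment would count as intervention effect. That goes too far. The plan compares changes from baseline, which removes stable differences in level. What stays confounded is kindergarten-specific change.
- **Error rates.** A reader might take 13%, 35% and 49% as the error rates of the stated plan. They are not. The abstract promises cluster-aware models, and the figures apply only to an unclustered analysis under an assumed ICC and an assumed equal split. A smaller ICC of change would shrink them.
- **Declaring success.** A reader might infer that the trial is bound to declare the intervention effective or not. The protocol sets a significance level but no such rule.
- **Abstract.** A reader might infer from "involving three kindergartens and up to 215 preschool children, their educators and parents" that the abstract presents all of these as the randomised comparison. It does not: its next sentence separates the pilot of about 75 children from the main phase.

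It could also be said that an analysis plan not shown here will settle the matter. It cannot. The number of kindergartens, the aim and the significance level are fixed in this article, and no analysis creates degrees of freedom that the design lacks.

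**Conclusion.** The point holds in this form: one kindergarten per arm fully confounds kindergarten-specific change over the 8–10 weeks with the intervention, and the between-kindergarten variance cannot be estimated. An effectiveness aim with p<0.05 between-arm tests is therefore unsupported, and describing the problem as power, generalisability and caution understates it.

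This conclusion needs no assumed ICC. It applies whenever kindergarten-level variance in change is above zero. The 0 degrees of freedom and the minimum randomisation p of 0.5 one-sided (1.0 two-sided) follow from the allocation alone. The type I errors and interval widths are illustrations that rest on the assumed ICCs and the assumed 70 children per kindergarten.

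The documents do not support a charge of concealment or of a misleading abstract.

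**What to change.** 1. Restate the first aim, for the main phase, as an exploratory or preliminary estimate of a between-kindergarten difference.
2. Remove p<0.05 decisions for all between-arm comparisons.
3. Report the baseline-adjusted difference with its CI, labelled as conditional on zero kindergarten-level variance in change. Beside it, give a sensitivity table of intervals over a range of assumed ICCs, such as 0.01, 0.05 and 0.10. The range is a convention with no source in the protocol and should be labelled so.
4. State in the limitations list and the Sample size section that arm and kindergarten are fully confounded: two kindergartens, about 140 children. A matching clarification in the abstract is optional.

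The cost is protocol and registry wording plus one table, with no new data. The downside is that the trial gives up a confirmatory effectiveness claim. Keeping that claim would require more kindergartens: at least four per arm before an unmatched cluster-level randomisation test can reach two-sided p<0.05, and more for adequate power. The main-phase randomisation is still described as lying ahead, so the choice can be made beforehand.
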